### Data and Safety Monitoring Plan

The P.I. and the research coordinator are responsible for ensuring absolute compliance with eligibility criteria and data confidentiality. All research materials will be kept locked in cabinets. Only the research team members will have a password to use the computer where the data will be acquired and stored. Adverse events are monitored by using Common Toxicity Criteria Manual of the National Cancer Institute as guidance, and reported to the Ethics Committee and to the NIH. Progress reports are sent to the Ethics Committee every 6 months. Serious adverse event reports must be reported to the Ethics Committee within 24 h.

## Discussion

This project represents a major step in developing a rehabilitation strategy with potential to have impact on the treatment of stroke patients with poor motor recovery in developing countries worldwide. The study preliminarily evaluates a straightforward, non-invasive, inexpensive intervention. If preliminary efficacy is demonstrated, further investigations of the proposed intervention (underlying mechanisms/ effects in larger samples of patients) should be performed.

The equipment used for RPSS has yet not received approval for clinical use in Brazil or in the United States. Most studies of RPSS included patients with mild motor impairments. After enrollment of this protocol had started, two studies about effects of RPSS in patients with mild to moderate impairments, conducted by the same group in the United States, were published (11, 45). In one, (45) 19 patients were randomized to 10 sessions of 2-h RPSS followed by 4-h modified constraint-induced therapy for the paretic upper limb, for 10 days. Significantly greater improvements in the WMFT, Action Research Arm Test (ARAT) and FMA-UL were documented after active (*n* = 9), compared to sham stimulation (*n* = 10). The differences in improvements in these outcomes between the groups were also statistically significant 1 month after the end of the intervention. In the other study, (11) 36 patients were included. Similar results were obtained. In addition, improvements in the active group were bigger than the minimal clinically important differences in the Active Research Test. These results were very encouraging, but the feasibility of a 6-h protocol of rehabilitation in the context of developing countries is challenging. Patients with moderate motor impairments often depend on caregivers in order to attend rehabilitation sessions, and the latter may not be able to remain at the health facility where treatment is provided, for a long period of time, over consecutive days. Also, administration of a 4-h modified constraint-induced movement therapy protocol may be a barrier to its implementation in clinical practice in developing and developed countries, considering the costs associated with payment of therapists to deliver treatments in a one-to-one basis over extended periods of time. This difficulty, as well as concerns about fatigue due to long periods of training, fostered development of modified, shorter protocols (46, 47) also shown to be beneficial to subjects in the chronic stage after stroke.

The proposed protocol will thus provide novel information about the effects of RPSS as an add-on intervention to motor training, under a protocol adapted to a developing-world environment, with shorter duration of treatment sessions, distributed over a longer period of time. Furthermore, the protocol has other differences in comparison to the paradigm applied by previous studies: (11, 46) first, recurrent strokes are included in the present protocol but were excluded by others (11, 46). Recurrent strokes are more common in developing countries such as Brazil compared to developed countries, and represented the most common reason for exclusion (45%) in a prior study of neuromodulation in stroke rehabilitation in Brazil (47). Because this protocol intended to be applied in a developing country, recurrent strokes were not excluded.

Second, while Carrico et al. (11) and Yadav et al. (46) administered RPSS to the Erb's point to provide brachial plexus stimulation, in addition to the median and radial nerves, in the current protocol RPSS is administered to the median, radial and ulnar nerves on the wrist/arm as previously reported (33). RPSS with Erb's point stimulation had not been described when the current protocol was designed, while nerve stimulation on the wrist/arm had been previously shown to be well-tolerated (10).

Follow-ups will continue up to 3 months post-treatment in the current protocol, providing information about long-term duration of effects of RPSS as an add-on intervention to treatment. Also, the evaluation of outcomes at 3 weeks aims to investigate whether 9 sessions of treatment lead to similar effects, compared to 18 sessions of treatment. If this hypothesis is proven correct, larger multicenter studies could be conducted faster, and at lower costs. According to current standards of payment of rehabilitation therapy and interventions of non-invasive peripheral stimulation in public health services in Brazil (http://sigtap.datasus.gov.br/tabela-unificada/app/sec/inicio.jsp), the costs of the entire treatment would be approximately 700 Brazilian reals (or 155 dollars).

Finally, detailed imaging data, including DTI analysis, is used in the proposed protocol in order to characterize the degree of involvement of the corticospinal tract, key to motor recovery after stroke, (48) in both the active and sham groups.

In summary, the results of the protocol “Peripheral Nerve Stimulation and Motor Training to Enhance Hand Function after Stroke” will advance the field of non-invasive neuromodulation for upper limb rehabilitation in stroke, a leading cause of disability worldwide.

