Six hours of daily rehabilitation for 10 days over 2 weeks may not be a feasible strategy in developing countries where the greatest disability from stroke occurs (12). Here, we report the design of the study “Peripheral Nerve Stimulation and Motor Training to Enhance Hand Function After Stroke” (ClinicalTrials.gov identifier NCT02658578). The aim of this study is to test the hypothesis that 3-h sessions of active RPSS associated with functional electrical stimulation (FES) and task-specific training (TST) distributed three times a week, over 6 weeks, is more beneficial to improve upper limb motor function than sham RPSS in addition to FES and TST, in subjects with moderate to severe hand motor impairments in the chronic phase after stroke.

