## Methods and Analysis

### Design

In this single-center, randomized, placebo controlled, parallel-group study we compare the effects of 18 sessions of active and sham RPSS as add-on interventions to FES and task-specific training of the paretic upper limb, in subjects in the chronic phase after stroke. Patients are naïve to the hypotheses of the study. Patients and researchers responsible for evaluation of outcomes are blinded to treatment allocation. Figure 1 shows the flow diagram of the trial.

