### Randomization, Allocation Concealment and Blinding

Subjects are randomized by the Principal Investigator (PI) with a basic random number computerized generator (randomization.com) in blocks of four, to active or sham RPSS in a 1:1 ratio. The randomization schedule is concealed in a locked cabinet accessed only by the PI and the investigators who administer RPSS.

Participants and investigators who assess outcomes are blinded to the interventions performed. Subjects are blinded to the experimental hypothesis and are not allowed to discuss their experience during the interventions with the researchers involved in assessment of outcomes or with other subjects. The clinical research forms of the blinded intervention are kept concealed in a locked cabinet. After each intervention session, subjects are asked: do you think your nerves were stimulated (yes/no)? Do you think your hand is different (worse/better/no change)?

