### Outcome Measures

The primary outcome measure is the Wolf Motor Function Test (WMFT) (40) after 6 weeks of treatment (end of treatment). The average time to perform 15 functional tasks (maximum, 120 s per task; if >120 s, the score is 121 s) as well as the quality of movement (Functional Ability Scale; range, 0 to 5) are assessed. The Minimal Clinically Important Differences (MCID) in the chronic phase are 1.2 to 2 s for the average time to complete the tasks, and 0.2 to 0.4 points for the Functional Ability Scale (41). The WMFT is a valid instrument with high interrater and test-retest reliabilities, as well as high internal consistency (42). The original version of the WMFT was developed to assess the effects of CIMT in stroke and traumatic brain injury.

The secondary outcomes are the WMFT at 3, 10 and 18 weeks after beginning of treatment, as well as the following outcomes measured at 3, 6, 10, and 18 weeks after beginning of treatment: MAL; active range of motion (ROM) of wrist extension and flexion; grasp and pinch strength in the paretic and non-paretic sides (the order of testing is randomized within and across subjects); MAS; FMA-UL in the paretic arm; BI; SIS; Beck Depression Inventory Short Form. Measurements assessed after 3 and 6 weeks of treatment are scheduled for days other than those in which the patients receive treatment, in order to avoid fatigue.

In addition, ROM of wrist extension and flexion is measured before and after the first session of treatment. ROM of wrist extension and flexion is measured with an analogic goniometer (ISP® Instituto São Paulo, São Paulo, Brazil) (43). Averages of three trials are calculated. Grip strength is measured with a Jamar dynamometer (Saehan Jamar, Changwong Korea) and pinch strength, with a digital dynamometer (Kratos, São Paulo, Brazil) (44). The trunk and the arms are stabilized and the wrist is kept in a neutral position during measurements.

All outcomes are evaluated by trained researchers blinded to the type of RPSS administered to patients. Assessments are videotaped.

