### Sample Size

We planned to include up to 40 patients and to determine the final sample size after evaluating the results of the first twenty patients included in the trial in regard to the MCID of the primary outcome (change in WMFT, Functional Ability Scale at 6 weeks compared to baseline).

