### Data Analysis

Analysis of variance with repeated measures or generalized estimating equations models with factors GROUP (active or sham) and TIME (baseline, 3, 6 weeks) will be performed, according to the distribution of the data. After all follow-ups have been completed, analyses will be performed with factors GROUP (active or sham) and TIME (baseline, 3, 6, 10, and 18 weeks). If there is an imbalance in Fugl-Meyer scores between the groups, then the analysis will be adjusted for baseline severity.

Also, the percentages of patients in the active and sham groups who will attain gains equal or larger than MCID in the WMFT and MAL, FMA-UL at 6, 10, and 18 weeks will be compared with chi-square tests or Fisher's exact tests.

Compliance with the interventions will be compared in the active and sham groups with Mann–Whitney tests.

Intention-to-treat (ITT) and per-protocol analyses will be performed. For intention-to-treat analysis, missing observations will be imputed with the Last Observation Carried Forward (LOCF).

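### Week 3 against week 6 cannot show that 9 sessions match 18: every patient is scheduled for 18, and the only stated analysis using week 3 tests for a difference

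*Protocol article*

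**What the plan says.** The Discussion gives the week-3 visit its own purpose: "evaluation of outcomes at 3 weeks aims to investigate whether 9 sessions of treatment lead to similar effects, compared to 18 sessions of treatment". The next sentence states the consequence: "If this hypothesis is proven correct, larger multicenter studies could be conducted faster, and at lower costs".

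The design has no group that receives 9 sessions. Under Design, "we compare the effects of 18 sessions of active and sham RPSS as add-on interventions to FES and task-specific training". The Introduction gives the schedule as sessions "distributed three times a week, over 6 weeks", and patients are randomised only "to active or sham RPSS in a 1:1 ratio".

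Data Analysis names a repeated-measures ANOVA or GEE model with "factors GROUP (active or sham) and TIME (baseline, 3, 6 weeks"), and later the same model with weeks 10 and 18 added. The comparisons of MCID responders are set at 6, 10 and 18 weeks and leave out week 3. Missing values in the intention-to-treat analysis are filled by LOCF. The section links no analysis to the 9-versus-18 question and names no similarity margin.

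On size, Sample Size says "We planned to include up to 40 patients and to determine the final sample size after evaluating the results of the first twenty patients". The only clinical benchmark for the primary scale is in Outcome Measures: an MCID of "0.2 to 0.4 points for the Functional Ability Scale". It is used for responders and for the sample-size review, not for this question.

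**The concern.** Two separate things stand between this aim and an answer.

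**Design.** Nobody is assigned to stop at 9 sessions. By week 3 a patient has had 9 sessions and 3 weeks; by week 6, 18 sessions and 6 weeks. The sham arm removes time trends common to both arms. It does not remove growth of the RPSS effect with time that would have occurred without the second 9 sessions. The trial can therefore describe response part-way through an 18-session course, but not what a 9-session programme would achieve at week 6 or later.

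**Analysis.** A GROUP and TIME model asks whether effects differ. Failing to find a difference is not evidence of similarity, and it happens most often when the data are noisy or few. A reader looking for the answer to the Discussion's question would find only this test.

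At stake is a side conclusion that could inform the length of treatment in later trials. The primary comparison at week 6 is not affected.

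**Working it through.** The article gives no SD, alpha, power or margin for this question, so there is no figure of its own to reproduce. The steps below check the schedule and then show how informative the week 3-to-6 comparison could be.

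**1. Schedule.** 3 sessions per week × 3 weeks = 9; 3 × 6 = 18. The session counts in the Discussion agree with the schedule in the Introduction.

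**2. Contrast.** The quantity that matches the randomised question is

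D = (active − sham at week 6) − (active − sham at week 3),

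which equals the between-arm difference in change from week 3 to week 6.

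**3. Inputs.**
- From the article: up to 40 patients at 1:1, so n = 20 per arm; MCID 0.2 to 0.4 points on the Functional Ability Scale (FAS).
- Assumed: SD of the week 3-to-6 change of 0.2, 0.3, 0.4 or 0.5 FAS points; two-sided 5% for the difference test; two one-sided 5% tests (a 90% CI inside the margin) for equivalence; no dropout.

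**4. Formulas.** SE = SD × √(2/20) = 0.316 × SD, with 38 df. The 95% CI half-width is 2.024 × SE. The chance of a non-significant result for a true D comes from the non-central t distribution with non-centrality D/SE. Equivalence power is the chance that the estimate ± 1.686 × estimated SE lies wholly within ±margin when the true D is 0.

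**5. Results at 20 per arm.**

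| Assumed SD | SE | 95% CI half-width | Non-significant if true D = 0.2 | Non-significant if true D = 0.4 | Equivalence power, margin 0.2 | Equivalence power, margin 0.4 |
|---|---|---|---|---|---|---|
| 0.2 | 0.063 | 0.13 | 13% | 0% | 86% | 100% |
| 0.3 | 0.095 | 0.19 | 46% | 2% | 33% | 99% |
| 0.4 | 0.126 | 0.26 | 66% | 13% | 3% | 86% |
| 0.5 | 0.158 | 0.32 | 77% | 31% | 0.1% | 60% |

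**6. If the trial stopped at its first 20 patients** (10 per arm, 18 df), a true D of 0.2 would be non-significant 44% of the time at SD 0.2 and 71% at SD 0.3.

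**7. Effect of LOCF.** A patient lost between weeks 3 and 6 has the week-3 value copied to week 6. That patient's change is exactly zero, which pulls this particular contrast towards no difference.

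**8. What the numbers do and do not settle.** They concern precision only. Even a CI tightly inside a margin would show that the active-minus-sham difference was much the same at weeks 3 and 6 in patients who were all continuing to 18 sessions. No sample size turns that into the effect of stopping at 9.

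**The case against.** The strongest reply has four parts.

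- **No misuse is stated.** A reader might infer that the trial plans to read a non-significant GROUP by TIME result as similarity. The article does not say so. It names the model factors and leaves the 9-versus-18 question unconnected to them. This objection stands: the misreading is a risk left open, not a rule in the plan. A margin or contrast could also sit in an analysis plan that is not shown. That answers the missing margin, but not the lack of a 9-session group, which is a fact of the design.
- **It is a side remark.** The question appears only in the Discussion, not in the stated aim, Sample Size or Data Analysis, and the study is presented as preliminary. A reader might also infer that the result would by itself shorten treatment in later trials. The text says only that such studies could be faster and cheaper. Both points stand and lower the severity.
- **Persistence is not claimed.** A reader might infer that the article means to show that a 9-session effect lasts to weeks 10 or 18. It does not, and the longer follow-up is tied to the treatment as delivered. Week 3 does measure outcome after 9 sessions, so comparing it descriptively with week 6 is legitimate.
- **The size depends on the benchmark.** At the lower MCID the comparison looks hopeless for SDs of 0.4 or more. At the upper MCID, 40 patients give equivalence power of 86% at SD 0.4. This stands, and both ends of the range have to be shown.

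What the reply does not remove is the wording. The Discussion calls this a hypothesis that can be proven, and neither the design nor the analysis stated can do that.

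**Conclusion.** The point holds in a limited form. The comparison of week 3 with week 6 is a mid-course comparison in which number of sessions is confounded with elapsed time, and the only stated analysis using week 3 is a difference test, which cannot establish similarity. The Discussion's wording claims more than this can deliver.

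The size depends on an SD that the article does not give. For assumed SDs of 0.2 to 0.5 FAS points at 20 per arm, the chance of missing a true added effect runs from 13% to 77% at the lower MCID and from 0% to 31% at the upper. Power to show equivalence when effects are truly equal runs from 86% down to 0.1% with a 0.2 margin, and from 100% down to 60% with a 0.4 margin. An equivalence reading of the interim contrast could thus be feasible or not, depending on margin and SD, but none is stated.

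Severity is minor to moderate: it concerns a side aim of a preliminary study and leaves the primary result untouched.

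**What to change.** 1. Report the week 3-to-6 change in the active-minus-sham FAS difference with its CI, taken from the model already planned, and read it against the article's MCID range of 0.2 to 0.4.
2. State that no similarity claim will be made from a non-significant test. If similarity is to be declared, do so only when the 90% CI lies within a margin fixed in advance from that range; otherwise call the result inconclusive.
3. Show this contrast also without values carried forward from week 3 to week 6, since those enter as zero change.
4. In the Discussion, replace the claim that the hypothesis could be proven with an exploratory statement about early response within an 18-session course, and say that it does not describe a 9-session programme.

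The cost is some wording, one contrast from the existing model and one sensitivity run. No visit, treatment or sample size changes. The price is a more modest claim, and the result may well be inconclusive.

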## Ethics Statement

The protocol, registered at clinicaltrials.gov (identifier, NCT02658578), was approved by the institutional and the Brazilian federal ethics committees (protocol 0546/11, CAAE 70163217.5.0000.0068). The study is being conducted according to the principles of the Declaration of Helsinki (49). Written informed consent is required from all participants or their legal representatives before inclusion.
